# **PLANTAR FASCIITIS STUDY PROTOCOL**

## **Background and Purpose**

Plantar fasciitis (PF) is the most common cause of heel pain and is estimated to affect 10% of the general population during their lifetime. During the years 1995 to 2000, PF accounted for 1 million patient visits per year to medical physicians in the United States. In 2007, the cost of treatment for PF in the United States ranged between \$192 and \$376 million. Electrical dry needling, manual therapy exercise and ultrasound, when applied separately, have each been found to be effective for PF. However, no previous study has investigated the combination of the effectiveness of electrical dry needling in addition to manual therapy, exercise and ultrasound in patients with PF. Therefore, the purpose of this multi-center randomized clinical trial is to compare the effects of adding electrical dry needling, into a program of manual therapy, exercise and ultrasound on pain and disability in individuals with PF. We hypothesize that individuals receiving electrical dry needling combined with manual therapy, exercise and ultrasound will exhibit greater improvements in pain and disability than those receiving only manual therapy, exercise and ultrasound.

## **Study Design**

Consecutive individuals with PF from outpatient physical therapy clinics in 6 U.S. states will be screened for eligibility criteria and recruited. For patients to be eligible, they need to meet the following criteria: 1, a clinical diagnosis of PF in accordance with the clinical practice guidelines from the American Physical Therapy Association; 2, plantar heel pain for longer than 3 months; 3, first-step pain in the morning during the previous week rated at least 2 on NPRS; and 4, aged 18 years or older. Patients will be excluded if any of the following criteria are present: 1, a history of surgery to the ankle, foot or lower leg; 2, contraindications to manual therapy, dry needling, exercise or ultrasound; 3, have had physical therapy, acupuncture, massage therapy, chiropractic treatment or local steroid injections for PF in the previous 4 weeks; 4, present with 2 or more positive neurologic signs consistent with nerve root compression; 5, have another cause of heel pain (including tarsal tunnel syndrome, calcaneal fracture, ankle or foot instability, arthritis of the foot or ankle, rheumatoid arthritis, neurogenic claudication, peripheral neuropathy); or 6, have involvement in litigation or worker's compensation regarding their heel pain. Patients will also be excluded if they are pregnant. All participants will sign an informed consent prior to participation in the study.

Following baseline examination, patients will be randomly assigned to receive manual therapy, exercise and ultrasound alone or combined with electrical dry needling. Concealed allocation will be conducted using a computer-generated randomized table of numbers. Individual and sequentially numbered index cards with the random assignment will be prepared for each of the data collection sites. The index cards will be folded and placed in sealed opaque envelopes. Blinded to the baseline examination, the treating physical therapist will open the envelope and proceed with treatment according to the group assignment.

All participants in both groups will receive up to eight treatment sessions at a frequency of once

or twice per week over a 4-week period. Both groups will receive an impairment-based manual therapy approach directed to the lower limb, an exercise program including self-stretching of the plantar fascia and the Achilles tendon and strengthening exercises for the intrinsic muscles of the foot, and therapeutic ultrasound (3 MHz, 1.5 W/cm^2, 20% duty cycle for 5 minutes to the most tender region of the proximal portion of the plantar fascia). Impairment-based manual therapy will be directed primarily to the foot/ankle, but also to the hip and knee, including but not limited to passive anterior to posterior talocrural joint mobilizations in weight-bearing and non-weight-bearing positions and/or distraction thrust talocrural joint manipulation to improve ankle dorsiflexion, subtalar joint lateral glide mobilizations for eversion and inversion, and anterior and posterior first tarsometatarsal joint glide mobilizations for pronation and supination of the midfoot. All patients in both groups will be instructed to complete a home exercise program during the 4-week treatment period. The home exercise program will consist of the same strengthening and stretching exercises prescribed in the clinic, but without supervision. Patients will be told to complete the home exercise program 3 times daily on the days that they do not receive supervised physical therapy in the clinic. Patients will be asked to monitor their compliance with the home exercise program using a logbook.

The experimental group will receive conventional physical therapy, as described above, plus electrical dry needling for 20 minutes. Dry needling will include the 8-point standardized electrical dry needling protocol. The technique will be performed with the patient in prone or side lying. Sterilized disposable stainless steel monofilament needles will be used with three sizes: 0.18 mm x 15 mm, 0.25 mm x 30 mm, 0.30 mm x 40 mm. The plantar and medial surface of the foot will be cleaned with alcohol. The following 8 needles will be inserted: (1) superoposterior and slightly lateral insertion angle toward the proximal attachment of the plantar fascia at the medial tubercle of the calcaneus. “Periosteal pecking” at or near the proximal attachment of the plantar fascia at the medial tubercle of the calcaneus, will be performed for 30 seconds over the most painful tender point at the medial calcaneal tubercle; (2) medial to lateral perpendicular insertion within the distal abductor hallucis, immediately plantar and proximal to the head of the first metatarsal—common myofascial trigger point location and perineural for the medial plantar nerve; (3) medial to lateral perpendicular insertion within the abductor hallucis, immediately plantar and distal to the base of the first metatarsal—common myofascial trigger point location and perineural for the medial plantar nerve; (4) medial to lateral perpendicular insertion, immediately inferior to the sustentaculum tali (approximately two fingerbreadths inferior to the inferior apex of the medial malleolus)—near the bifurcation point of the tibial nerve and posterior tibial artery; (5) medial to lateral perpendicular insertion in the depression midway between the prominence of the medial malleolus and the Achilles tendon—perineural point for the tibial nerve at the ankle; (6) plantar to dorsal perpendicular insertion in the mid belly of flexor digitorum brevis and quadratus plantae muscles, two to three fingerbreadths distal to the anterior and plantar border of the calcaneus—common myofascial trigger point within the flexor digitorum brevis and perineural stimulation for the lateral plantar nerve; (7) plantar to dorsal perpendicular insertion within the distal plantar aponeurosis near its attachment at the metatarsophalangeal plates, within the depression on sole of the foot one third of the distance from the tip of the second toe to the posterior calcaneus; (8) medial to lateral perpendicular insertion within the abductor hallucis, within the depression immediately plantar to the navicular tuberosity—common myofascial trigger point and perineural for the medial plantar nerve.

In addition to the 8-point standardized protocol, therapists will also be permitted to insert needles at up to 4 additional locations in the foot and/or lower leg based on the presence of trigger points, or the report of sensitivity by the patient. The medial head of the gastrocnemius is recommended as one of the four optional needle insertion sites. Following insertion, needles will be manipulated bi-directionally to elicit a sensation of aching, tingling, deep pressure, heaviness or warmth, and then left in situ for 20 mins with electric stimulation (ES-160 electrostimulator ITO co.) using a low frequency (2 Hz), moderate pulse duration (250 microseconds), biphasic continuous waveform at an intensity described by the patient as “mild to moderate”.

The primary outcome will be first-step pain during the morning as measured by the Numeric Pain Rating Scale (NPRS). Secondary outcomes will include resting mean foot pain (NPRS), pain during activity (NPRS), the Lower Extremity Functional Scale (LEFS), the Foot Functional Index (FFI), medication intake, and the Global Rating of Change (GROC) at baseline, 1 week, 4 weeks and 3 months. Medication intake will be measured as the number of times the patient has taken prescription or over-the-counter analgesic or anti-inflammatory medication in the past week for their heel pain, with five options: (1) not at all, (2) once a week, (3) once every couple of days, (4) once or twice a day, or (5) three or more times a day. Medication intake will be assessed at baseline and at 3 months. In addition, the Global Rating of Change (GROC) will be collected at 1 week, 4 weeks and 3 months following the initial treatment session.

In order to detect treatment differences of 2 points on the main outcome (i.e. the MCID for NPRS on first-step pain), and assuming a standard deviation of 3 points, a 2-tailed test, an alpha level of 0.05 and a desired power of 90%, the estimated desired sample size is calculated to be at least 49 subjects per group. A dropout percentage of 10% is expected, so 53 patients will be included in each group.

Statistical analyses will be performed using SPSS and conducted according to intention-to-treat analysis for patients in the group to which they are first allocated. Mean, standard deviations and/or 95% confidence intervals will be calculated for each variable. Baseline demographic and clinical variables will be compared between both groups using independent Student t-tests for continuous data and  $\chi^2$  tests of independence for categorical data. The effects of treatment on first-step pain intensity, resting foot pain, pain during activity, physical function, and related-disability will each be examined with a 2-by-4 mixed model analyses of covariance (ANCOVA) with treatment group (conventional physical therapy vs. conventional physical plus electrical dry needling) as the between-subjects factor, time (baseline, 1 week, 4 weeks and 3 months follow-up) as the within-subjects factor, and adjusted for baseline data for evaluating between-groups differences. Separate ANCOVAs will be performed for first-step pain intensity, mean heel pain at rest, pain during activity, the Lower Extremity Functional Scale, the FFI Total Score, the FFI Pain Subscale, the FFI Disability Subscale, and the FFI Activity Limitation Subscale as the dependent variable. For each ANCOVA, the main hypothesis of interest will be the 2-way interaction (group by time) with a Bonferroni-corrected alpha of 0.0125 (4 time points). We will use  $\chi^2$  tests to compare self-perceived improvement with GROC and changes in medication intake. To enable comparison of between-group effect sizes, standardized mean score differences (SMDs) will be calculated by dividing mean score differences between groups by the pooled standard deviation. Numbers needed to treat and 95% confidence intervals will also be calculated at the 3-months follow-up period using each definition for a successful outcome.

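### Allocation cards are prepared site by site, but the stated ANCOVA has no site term: a modest precision and design-alignment point, not a validity error

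*Protocol*

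**What the plan says.** The Protocol calls itself a multi-centre trial in Background and Purpose ("the purpose of this multi-center randomized clinical trial"). Study Design recruits from "outpatient physical therapy clinics in 6 U.S. states" without giving the number of sites.

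On allocation, Study Design says: "Concealed allocation will be conducted using a computer-generated randomized table of numbers". It then says: "Individual and sequentially numbered index cards with the random assignment will be prepared for each of the data collection sites". Each site thus has its own numbered sequence. Blocking is not mentioned, and site is not named as a stratification factor.

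On analysis, the statistical paragraph of Study Design specifies a "2-by-4 mixed model analyses of covariance (ANCOVA) with treatment group" as the between-subjects factor, time as the within-subjects factor, and adjustment for the baseline value. Site, clinic and therapist do not appear in that model, in the chi-square tests for GROC and medication intake, or in the sample-size paragraph.

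**The concern.** When patients are allocated from site-specific lists, the analysis would normally condition on site. Outcomes may well differ between clinics here. The treatment common to both arms is hands-on and adapted to each patient's impairments, the number of sessions can vary, and needling allows optional extra points. Any such between-site variation stays in the residual of a model without site.

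This is more than a detail left to a SAP. The Protocol lists the model's factors, their levels, the covariate and the alpha, so adding site changes a stated model. What is at stake is precision and agreement between design and analysis. A site term added after the results are known would also look post hoc.

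**Working it through.** **Inputs from the Protocol (Study Design, sample-size paragraph).** Difference 2 NPRS points, SD 3, two-sided alpha 0.05, power 90%, 49 evaluable patients per group.

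**Assumptions, because the Protocol gives no figure.** The between-site share of outcome variance, ρ, is taken as 0 to 0.20. The number of sites is taken as 6 equal sites or, alternatively, 10 sites of 10 patients.

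**Step 1: reproduce the stated sample size.** n = 2 × 3² × (1.960 + 1.282)² / 2² = 47.3, so 48 by the normal approximation. The t-test solution is 48.26, rounded up to 49. The stated figure reproduces.

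At 49 per group, SE = 3 × √(2/49) = 0.606 and 2/0.606 = 3.30. Power is Φ(3.30 − 1.96) = 0.910.

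**Step 2: lists balanced within site.** Balance removes site differences from the treatment contrast, so the true SE is 0.606 × √(1−ρ). The unadjusted test still uses about 0.606. Hence:

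- true alpha without site = 2 × [1 − Φ(1.96/√(1−ρ))]
- power without site = Φ((3.30 − 1.96)/√(1−ρ))
- power with site = Φ(3.30/√(1−ρ) − 1.96)

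| ρ (assumed) | True alpha, no site | Power, no site | Power, with site | Gain (points) |
|---|---|---|---|---|
| 0.02 | 0.048 | 0.912 | 0.915 | 0.3 |
| 0.05 | 0.044 | 0.915 | 0.923 | 0.8 |
| 0.10 | 0.039 | 0.921 | 0.936 | 1.4 |
| 0.20 | 0.028 | 0.933 | 0.958 | 2.5 |

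A simulation with blocks of 4 in 6 sites (98 patients, 6,000 runs per cell) agrees on power: 0.911 without site against 0.919 with it at ρ = 0.05, 0.917 against 0.931 at 0.10, and 0.932 against 0.955 at 0.20.

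**Step 3: unrestricted lists per site.** The (1−ρ) shortcut no longer applies. Unequal splits within sites cost a fixed-site analysis some efficiency, and chance site imbalance is already part of the unadjusted standard error. Simulated power (6,000 runs per cell):

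| ρ (assumed) | 6 sites: no site / with site | 10 sites of 10: no site / with site |
|---|---|---|
| 0 | 0.905 / 0.885 | 0.911 / 0.879 |
| 0.02 | not run | 0.908 / 0.882 |
| 0.05 | 0.908 / 0.902 | 0.912 / 0.894 |
| 0.10 | 0.913 / 0.919 | 0.906 / 0.904 |
| 0.20 | 0.900 / 0.937 | not run |

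The simulation standard error of a power near 0.90 is √(0.9 × 0.1/6000) = 0.004, so differences of half a point are noise. Type I error without site was 0.051 to 0.053 with 6 sites. With 10 sites it was 0.045 to 0.058 (3,000 runs each). It is preserved.

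**Limits of the check.** It compares a single follow-up value at alpha 0.05, as the sample-size paragraph does. It does not model the group-by-time interaction at 0.0125. A site difference that is constant over time cancels from that interaction, so for that test ρ means the share due to site differences in change over time. Baseline adjustment may also absorb some site variation. Both limits are reasons not to expect more than the figures above.

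**The case against.** The strongest case against runs as follows. Per-site cards may be no more than envelope logistics, since site is never named as a stratification factor. Block sizes and pooling rules commonly sit in a SAP or randomisation specification. Under unrestricted lists with many small sites, adding fixed site effects can lower power. Most of this stands. It limits the point to a small precision gain, and silence on blocking is not itself an error. It does not remove the point: allocation does run from site-specific sequences, and the stated model does omit site.

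Three stronger readings are tempting, and the documents support none of them.

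- **Site or therapist differences bias the comparison.** A reader might infer this from the chance of uneven splits. A hypothetical 10-patient site with an unrestricted list has a 2 × (1 + 10 + 45 + 120)/1024 = 34% chance of a 7:3 or worse split. Such imbalance is ordinary randomisation error, covered by the unadjusted standard error. The figure also presupposes unrestricted lists, which the Protocol's silence does not establish.
- **This is clustering that inflates type I error.** Site is crossed with arm, not nested in it, so no cluster design effect applies. The treating therapist opens the envelope and treats as assigned, which suggests that therapists also treat both arms. The Protocol does not say so outright and gives nothing from which a therapist effect could be quantified.
- **A site term is free and always raises power.** Step 3 of the working shows otherwise.

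**Conclusion.** The point holds as one of precision and design alignment. The Protocol prepares assignments by site and specifies an analysis that does not use site. The omission does not invalidate the treatment estimate, the test or the 49 per group.

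With balanced lists, the unadjusted test errs on the safe side and forgoes at most about 2.5 points of power over the assumed range of ρ. With unrestricted lists, the sign of the effect depends on site size and on ρ: a loss of about 1 to 3 points when ρ is small, roughly break-even between 5% and 10%, and a gain above that.

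These sizes rest on assumed values of ρ and of the number of sites. The facts about allocation and model terms rest on the text alone. Severity is optional to moderate.

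**What to change.** 1. State whether the site lists are blocked. Generate any lists not yet issued as permuted blocks of varying size within site.
2. Add site to each ANCOVA. Pool small sites by state under a rule fixed before unblinding, or fit site as a random intercept if sites are many and small. Because the main hypothesis is the group-by-time interaction, say whether site is also crossed with time; a site main effect alone does little for that test.
3. If the lists already issued prove to be unrestricted and the sites small, prefer pooling or the random intercept to one fixed effect per site, given the losses in step 3 of the working.

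The cost is a few degrees of freedom (how many cannot be said, because the number of sites is not given), slight predictability from blocking that varying block sizes limits, and a possible small loss of power if site variance is negligible. It needs each patient's site on the analysis file, no extra patients, and no increase in the 49 per group.

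### The sample size gives 90% power at two-sided alpha 0.05, but the main hypothesis is to be declared at 0.0125, so the stated power is not supported at the trial's own threshold

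*Protocol*

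**What the plan says.** Everything relevant stands in the Study Design section of the protocol.

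- **Primary outcome:** "The primary outcome will be first-step pain during the morning as measured by the Numeric Pain Rating Scale (NPRS").
- **Sample size inputs:** "In order to detect treatment differences of 2 points on the main outcome", "assuming a standard deviation of 3 points", and "a 2-tailed test, an alpha level of 0.05 and a desired power of 90" per cent.
- **Result:** "the estimated desired sample size is calculated to be at least 49 subjects per group".
- **Dropout:** "A dropout percentage of 10% is expected, so 53 patients will be included in each group".
- **Decision rule**, in the analysis paragraph, for each ANCOVA: "the main hypothesis of interest will be the 2-way interaction (group by time) with a Bonferroni-corrected alpha of 0.0125 (4 time points").

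First-step pain is one of the dependent variables listed for these ANCOVAs, so the 0.0125 threshold applies to the primary outcome. The model is a 2-by-4 mixed-model ANCOVA adjusted for baseline. The sample size paragraph mentions neither the stricter threshold nor any correlation between repeated measurements.

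**The concern.** The alpha used to size the trial is four times the alpha used to judge it (0.05 / 0.0125 = 4). Power is a property of a test at a given threshold, so a figure computed at 0.05 cannot be quoted for a decision made at 0.0125. An unseen analysis plan could not fill this as if it were a gap, because the protocol fixes both numbers itself.

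Two things are at stake. A primary p-value between 0.0125 and 0.05 would count as success at the level used for sizing and as failure at the level used for analysis. And a non-significant primary result would be reported as coming from a trial with 90% power, although that figure was never worked out for the threshold applied.

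**Working it through.** **Inputs from the protocol:** difference 2 points, SD 3 points, two-sided test, alpha 0.05 for sizing and 0.0125 for testing, 49 evaluable and 53 enrolled per group, 10% dropout. Evaluable patients after dropout: 53 × 0.90 = 47.7 per group.

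**Method.** Two-sample t-test with n per group, df = 2n − 2 and noncentrality δ = 2 / (3 × √(2/n)). Power is the probability that a noncentral t variable with these df and this δ exceeds the two-sided critical value t(1 − α/2, df) in absolute size.

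**Step 1: reproduce the plan's figure.** At alpha 0.05, n = 48 gives 89.8% and n = 49 gives 90.4%. The smallest n reaching 90% is therefore 49, exactly as stated. (The normal approximation would give 48.) This identifies the sizing method as an unadjusted two-sample t-test.

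**Step 2: same test and inputs at alpha 0.0125.** For n = 49, δ = 2 / (3 × √(2/49)) = 2 / 0.606 = 3.30. The critical value rises from 1.985 to 2.546.

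| n per group | Power at 0.05 | Power at 0.0125 |
|---|---|---|
| 47.7 (53 less 10%) | 89.7% | 75.9% |
| 49 | 90.4% | 77.3% |
| 53 (no dropout) | 92.5% | 81.1% |

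- The smallest n for 90% power at 0.0125 is 66 evaluable per group. With 10% dropout, 66 / 0.90 = 73.3, so 74 enrolled.
- The difference detectable with 90% power at 0.0125 is 2.33 points (n = 49) to 2.36 points (n = 47.7).
- Dividing by the three follow-up visits alone (0.05 / 3 = 0.0167) would give 79.2% (n = 47.7) to 80.4% (n = 49), still short of 90%.

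**Step 3: what baseline adjustment could recover.** The protocol gives no baseline-to-follow-up correlation r, so the values below are assumptions. For one adjusted contrast at one visit, the residual SD is 3 × √(1 − r²) and one further degree of freedom is lost. At alpha 0.0125, with n from 47.7 to 49:

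| Assumed r | Residual SD | Power at 0.0125 |
|---|---|---|
| 0.3 | 2.86 | 80–82% |
| 0.5 | 2.60 | 88–89% |
| 0.6 | 2.40 | 93–94% |
| 0.7 | 2.14 | 98% |

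The break-even for 90% is r of about 0.51 to 0.53.

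**Step 4: the interaction test itself.** Assume an omnibus 3-df group-by-time test with compound symmetry at correlation r. The noncentrality is λ = (n/2) × Σ(dᵢ − d̄)² / (9 × (1 − r)), where dᵢ are the group differences at the four visits, with df 3 and 3 × (2n − 2). With 48 to 49 per group at 0.0125:

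| Differences at the four visits | r = 0.3 | r = 0.5 | r = 0.7 |
|---|---|---|---|
| 0, 2, 2, 2 | 64–65% | 83–84% | 98% |
| 0, 0.67, 1.33, 2 | 46–48% | 66–67% | 91–92% |

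At alpha 0.05 the first pattern gives 81–82%, 93–94% and over 99%. The result depends on the correlation and on the shape of the effect over time, and the protocol states neither.

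**The case against.** The strongest reply is that 76–77% is itself the power of a test the trial does not plan. The planned analysis adjusts for baseline and tests an interaction. If the relevant correlation were above roughly 0.5, a single adjusted contrast at 0.0125 would reach 90% or more with the planned numbers, and at r = 0.7 the omnibus test would as well under both patterns shown. This stands. A reader might infer that the trial really has 76–77% power, or that its true false-negative risk has more than doubled. The document does not support that as a statement about the planned analysis: the true figure could be lower or higher. Nor may one pick r = 0.5 alone and conclude that power stays below 90%, since that value lies just under the break-even.

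It can also be said that the stricter threshold is conservative. It neither inflates the type I error nor biases the estimate, and 49 is correctly computed for the test it assumes. That is true as well, and it limits the finding to the power statement and the decision rule.

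What the reply does not do is rescue the 90%. The sample size paragraph claims no gain from correlation, so crediting one now would bring in an assumption that the protocol does not make.

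**Conclusion.** The point holds as an inconsistency between the planning alpha and the testing alpha for the primary outcome. The stated 90% power is unsupported at 0.0125. On the plan's stated inputs and its own sizing method, an unadjusted two-sample t-test, power at that threshold is about 76–77%, a type II error of about 23–24% for that test against the planned 10%. These figures rest on difference 2, SD 3 and 47.7 to 49 evaluable patients per group.

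The finding does not show that the planned ANCOVA is underpowered. That would need the within-patient correlations and the expected course of the effect over the visits. It does show that the protocol gives no basis for 90% at the threshold it sets, on the outcome that decides the trial.

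**What to change.** Before outcome data are seen, do one of the following for first-step pain:

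1. **Test one pre-specified primary hypothesis at two-sided 0.05.** A single interaction test on the one primary outcome does not need division by four time points, so the correction can be dropped for that test. If a contrast at one visit is preferred, the sponsor should choose the visit and state it, since the protocol names no primary time point. On the stated inputs an unadjusted single-visit comparison at 0.05 has 89.7–90.4% power. For the interaction test, aligning the alpha removes the contradiction, but a power figure still needs stated correlation and effect-pattern assumptions.
2. **Keep 0.0125 and restate the power** as about 76–77% on the stated inputs, or the detectable difference as about 2.3–2.4 points.
3. **Keep 0.0125 and state the correlation assumption** that justifies a higher figure, with its basis and a range around it.

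None of these needs more patients. Options 2 and 3 are changes to the sample size text; option 2 costs a less favourable stated power. Option 1 changes the threshold of the primary test. Choosing a single visit goes further: it is a design decision, not a matter of wording only. Keeping both 0.0125 and 90% power without any credit for correlation would need 66 evaluable per group, about 74 enrolled, against the planned 53.

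### Baseline is both a level of the time factor and the covariate, so the primary ANCOVA is mis-specified and its named test changes with an unstated modelling choice

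*Protocol*

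**What the plan says.** The analysis paragraph at the end of Study Design in the protocol sets out one model for every continuous outcome, a "2-by-4 mixed model analyses of covariance (ANCOVA"). Its repeated factor and its adjustment are given together as "time (baseline, 1 week, 4 weeks and 3 months follow-up) as the within-subjects factor, and adjusted for baseline data for evaluating between-groups differences". So baseline is one of the four outcome levels and also the covariate.

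Eight dependent variables get this model: first-step pain, which is the primary outcome, and seven others. For each, "the main hypothesis of interest will be the 2-way interaction (group by time"), tested at a "Bonferroni-corrected alpha of 0.0125 (4 time points"). The group main effect is not named as a test. The text does not say whether the covariate has one slope or one per visit, or whether the interaction is read from the univariate or the multivariate test.

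**The concern.** A pre-treatment value can serve as an outcome level or as a covariate. Used as both, it is regressed on itself. The model then either contains a level with no information and no error, or carries an adjustment that never reaches the tested term.

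This is not detail left to a statistical analysis plan. The protocol itself fixes the time levels, the covariate, the tested term and the alpha, and they do not fit together. At stake is what the primary p-value tests, and whether the choice between quite different tests is made before or after the data are seen.

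**Working it through.** **Inputs.** From Study Design: difference 2 points, SD 3, 49 evaluable per group, two-sided alpha 0.05 and 90% power for the sample size; alpha 0.05/4 = 0.0125 for the interaction. The protocol gives no between-visit correlation. I assume compound symmetry with ρ = 0.3, 0.5 and 0.7, and a constant 2-point benefit at all three follow-ups.

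**The plan's own figure.** n = 2(1.960 + 1.282)² × 3²/2² = 47.3, so 48 per group by the normal formula. The exact t-test gives 49, with power 90.4%. The stated 49 is reproduced, but for one two-group comparison at 0.05, not for an interaction at 0.0125.

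**Reading A: one slope per visit.** Write Y(t) = a(t) + d(t)·group + b(t)·Y(0) + error.
- At baseline, Y(0) is regressed on Y(0). So b(0) = 1, and d(0) and every residual are exactly 0.
- Equality of all four d(t) therefore means that the three follow-up differences are all 0. The multivariate interaction test is a joint 3-df test of the adjusted follow-up differences; in simulation the two p-values agreed to about 1e-14. Its type I error at nominal 0.05 was 4.4-5.4%.
- Residual variance is 0 at baseline and 9(1 − ρ²) at each follow-up: 8.19, 6.75 and 4.59. Sphericity needs every pairwise difference of residuals to have the same variance. Baseline against a follow-up has 9(1 − ρ²); two follow-ups have 18(1 − ρ). The ratio is 2/(1 + ρ) = 1.54, 1.33 and 1.18, and reaches 1 only at ρ = 1. So sphericity cannot hold under compound symmetry. With other patterns it would need the follow-up residuals to correlate at exactly 0.5. The simulated size of the univariate test was 0.012-0.018 at nominal 0.0125.
- The group effect averaged over four levels is (0 + 2 + 2 + 2)/4 = 1.5, against 2.0 over the three follow-ups. The standard error shrinks by the same factor of 3/4, so the p-value is identical.

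**Reading B: one common slope.** In Y(t) − Y(0), the term b·Y(0) appears twice and cancels. The interaction is then the unadjusted comparison of changes from baseline. With group differences (0, 2, 2, 2), the squared deviations from 1.5 sum to 2.25 + 3 × 0.25 = 3. The noncentrality is (49/2) × 3/[9(1 − ρ)] = 11.7, 16.3 and 27.2. The noncentral F with 3 and 288 df gives power 65%, 84% and 98%; simulation gave 66%, 84% and 98%, and 62%, 83% and 98% for the multivariate version.

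**Comparator: adjusted difference averaged over the three follow-ups.** Variance per patient is 9(1 + 2ρ)/3 − 9ρ² = 3.99, 3.75 and 2.79. SE = √(2 × variance/49) = 0.404, 0.391 and 0.337. z = 2/SE = 4.96, 5.11 and 5.93, against a critical value of 2.50.

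| Power at alpha 0.0125 | ρ = 0.3 | ρ = 0.5 | ρ = 0.7 |
|---|---|---|---|
| Interaction, common slope | 66% | 84% | 98% |
| Interaction, slope per visit, univariate | 83% | 93% | 99% |
| Interaction, slope per visit, multivariate | 96% | 97% | 99% |
| Adjusted difference at 3 months only | 81% | 90% | 98% |
| Adjusted difference averaged over follow-ups | 99% | 99% | >99% |

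**Dropping baseline but keeping the interaction test.** With three post-baseline levels, a constant 2-point benefit gave a significant interaction in only 1.2-1.5% of runs at 0.0125, which is no more than chance.

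**The case against.** A reader might infer that the primary treatment effect will be understated by 25%. The documents do not support that. The shrinkage from 2.0 to 1.5 affects only a group effect averaged over all four levels, and the protocol tests the interaction. That test is not diluted, the adjusted 3-month difference stays at 2.0 points, and even the averaged effect keeps its p-value.

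A reader might also infer that the planned test is badly underpowered or invalid. That too goes beyond the evidence. Power near 80% under Reading A arises only for the univariate test at ρ = 0.3. The multivariate test keeps 96% or more. Type I error stays near nominal, and a sphericity correction is routine and may sit in an analysis plan that is not shown.

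Nor is the comparison with the averaged contrast like for like: a constant effect favours a 1-df average over a 3-df test. Against the adjusted difference at 3 months alone, the Reading A interaction is no weaker. The coherent alternative of baseline as an outcome level without a covariate has the power of Reading B, so double use does not by itself cost power.

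All of this stands, and it limits the harm. It does not remove the contradiction: on one reading the stated adjustment acts on the tested term, on the other it does not, and the protocol does not say which applies.

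**Conclusion.** The point holds as a specification error with an ambiguous primary test, not as a biased or invalid one. Baseline is both outcome level and covariate in all eight ANCOVAs. For the protocol's own 2-point effect, SD and group size, power at 0.0125 runs from about 66% to 96% at ρ = 0.3, from 84% to 97% at 0.5, and hardly varies at 0.7. Several readings miss the 90% that the sample size was built for. These figures rest on assumed correlations, compound symmetry, complete data on 49 per group and a constant benefit. The algebra (zero residual at baseline with a slope per visit, cancellation with a common slope) does not depend on the correlations. The alpha divisor of 4 also counts baseline, where no treatment effect can exist.

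**What to change.** Amend the analysis paragraph before any analysis:

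- Make time a 3-level post-baseline factor (1 week, 4 weeks, 3 months), with the outcome's own baseline value and a baseline-by-time term as covariates.
- Make the primary test the baseline-adjusted group difference, and state now whether it is the average over the follow-ups or the difference at one named visit.
- Do not keep the group-by-time interaction as the primary test once baseline leaves the time factor, because it cannot see a constant benefit.
- Replace the divisor of 4: no division for a single prespecified contrast, or 0.05/3 = 0.0167 if all three visits are tested.

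A single contrast at 0.05 also brings the analysis into line with the alpha used for the sample size. For the 3-month difference alone, SE = √(2 × 9(1 − ρ²)/49) = 0.578, 0.525 and 0.433. So z = 3.46, 3.81 and 4.62, and power by the normal approximation is about 93%, 97% and over 99%.

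The cost is a short amendment, with no new data and no additional patients. The one real change is that the stated main hypothesis moves from the interaction to a group contrast, which is why it must be made before the results are known.
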